### IFN $\gamma$ +IL2-TNF $\alpha$ + CD4 T cell responses to Ag85B

[figure not shown]

### IFN $\gamma$ +IL2-TNF $\alpha$ + CD4 T cell responses to ESAT-6

[figure not shown]

**Supplementary Figure 8. Cytokine responses for all study groups at all time points.** Descriptive line plots of cytokine responses measured by flow cytometry (WB-ICS assay) from day 0 to day 238 with median and IQR for all study groups etoricoxib-group (red, n=10), H56:IC31-group (blue, n=12), controls (black, n=10) and etoricoxib+H56:IC31 group (green, n=8) are depicted for all possible combinations of Cytokine+ T-cells to the individual *Mtb* peptides ESAT-6, Ag85B and Rv2660c and all peptides combined.

# PROTOCOL SYNOPSIS

|                                                                                                                                                                                                                                                                                                                                                                                                                                                                                                                                                                                                                                                                                                                                                                                                                                                                                                                                                                                                                                                                                                                                                                                                 |
|-------------------------------------------------------------------------------------------------------------------------------------------------------------------------------------------------------------------------------------------------------------------------------------------------------------------------------------------------------------------------------------------------------------------------------------------------------------------------------------------------------------------------------------------------------------------------------------------------------------------------------------------------------------------------------------------------------------------------------------------------------------------------------------------------------------------------------------------------------------------------------------------------------------------------------------------------------------------------------------------------------------------------------------------------------------------------------------------------------------------------------------------------------------------------------------------------|
| Name of Sponsor/Company: Oslo University Hospital                                                                                                                                                                                                                                                                                                                                                                                                                                                                                                                                                                                                                                                                                                                                                                                                                                                                                                                                                                                                                                                                                                                                        |
| Name of Products: Arcoxia (MSD). Tuberculosis vaccine: H56:IC31                                                                                                                                                                                                                                                                                                                                                                                                                                                                                                                                                                                                                                                                                                                                                                                                                                                                                                                                                                                                                                                                                                                          |
| Name of Active Ingredient: etoricoxib. H56 antigen and IC31 adjuvant.                                                                                                                                                                                                                                                                                                                                                                                                                                                                                                                                                                                                                                                                                                                                                                                                                                                                                                                                                                                                                                                                                                                    |
| Title of Study: Therapeutic vaccination and immune modulation - new treatment strategies for the multidrug-resistant tuberculosis pandemic. A open label phase I clinical trial of the therapeutic TB H56:IC31 vaccine and cyclooxygenase-inhibitors (COX-2i)                                                                                                                                                                                                                                                                                                                                                                                                                                                                                                                                                                                                                                                                                                                                                                                                                                                                                                                     |
| EudraCT nr: 2014-004986-26.                                                                                                                                                                                                                                                                                                                                                                                                                                                                                                                                                                                                                                                                                                                                                                                                                                                                                                                                                                                                                                                                                                                                                              |
| Protocol Identification Number: TBCOX2                                                                                                                                                                                                                                                                                                                                                                                                                                                                                                                                                                                                                                                                                                                                                                                                                                                                                                                                                                                                                                                                                                                                                   |

| Objectives: 
 
1. Study the safety and tolerability of etoricoxib given for 20 weeks (day 0-140) alone and in combination with the therapeutic TB vaccine H56:IC31 given as two immunizations at day 84 and day 140 in patients with active TB disease treated with conventional 26-week anti-TB chemotherapy.
 
2. Study the immune effects of etoricoxib given for 20 weeks (day 0-140) on immune regulation and TB vaccine (H56:IC31) immunogenicity in patients with active TB disease treated with conventional 26-week anti-TB chemotherapy.
 
                                                                                                                                                                                                                                                                                                                                                                                                                                                                                                                                                     |
| Methodology: Open-label controlled, randomized study                                                                                                                                                                                                                                                                                                                                                                                                                                                                                                                                                                                                                                                                                                                                                                                                                                                                                                                                                                                                                                                                                                                                     |
| Number of Subjects Planned: A total of 40 patients with active pulmonary and/or extra-pulmonary TB disease infected with drug-sensitive Mtb strains will be included sequentially in two groups A and B. Group A comprises the following study arms: Arm #1, etoricoxib (n=10), Arm #2 H56:IC31 TB vaccine (n=10) and Arm #3 as controls (n=5). Following safety review at day 98 we will include for part B comprising Arm #4 H56:IC31 TB vaccine and etoricoxib (n=10) and the remainder of controls for Arm #3 (n=5).                                                                                                                                                                                                                                                                                                                                                                                                                                                                                                                                                                                                                                                          |
| Diagnosis and Main Criteria for Inclusion: 
 
1. Age between 18 and 70 years at the time of randomization
 
2. Microbiologically confirmed pulmonary TB (culture and/or PCR + susceptibility testing) and/or microbiologically confirmed extra-pulmonary TB (culture and/or PCR + susceptibility testing)
 
3. Drug sensitive Mtb strains (except single resistance where fully adequate anti-TB chemotherapy regimen could be provided).
 
4. Is willing and likely to comply with the trial procedures and is prepared to grant authorized persons access to their medical record.
 
5. Has completed the written informed consent process prior to the start of screening evaluations.
 
6. Females: Ability to avoid pregnancy during the trial.
 
 Subjects may receive H56:IC31 vaccination (study arm 2 and 4) if they meet the following criteria: 
 
1. Sputum obtained prior to 1th immunization (day 84) must be Mtb negative evaluated by at least two consecutive AFS or PCR/GeneXpert at least 7 days apart.
 
 |

2. Documented reduction in the extent of TB disease at the infectious site(s) within day 84 evaluated by physical and/or radiological examination (table A2).
3. Clinical improvement with normal vital signs (blood pressure, temperature and pulse), improvement of any TB related symptoms to Grade 1-3 (table A2), stable or increased body-weight and reduced inflammatory blood parameters (CRP, ESR and WBC counts) compared to baseline.

**Main exclusion criteria:**

**(i) Study-specific:** Disseminated TB. Evidence of a new acute illness that may compromise the safety of the subject in the trial on study day 0. History of autoimmune disease or immunosuppression. History or laboratory evidence of any possible immunodeficiency state. Anemia (<9 g/100 ml). HIV sero-positivity. Chronic hepatitis B (HBs antigen positive) with increased liver transaminases (ASAT, ALAT) or chronic hepatitis C (HCV RNA positive). Concomitant or sporadic use of NSAID or corticosteroids (>2 times per week). Other immune modulating therapies including DMARDS. Total cholesterol > 7 mmol/L. Hypertension >140/90 mm Hg (treated or untreated) or treated with >1 antihypertensive drug at any blood pressure. Cardiovascular events or stroke in parents, siblings or off-springs occurring < 55 years of age. Serum creatinine above reference levels (females > 90 µmol/L; males > 105 µmol/L). Known diabetes mellitus type I or diabetes mellitus type II with HbA1c >7%. Pregnancy (S-hCG >5 IU/l for females at childbearing age). Breastfeeding.

**(ii) Exclusion criteria for etoricoxib according to SPC:** Known hypersensitivity for etoricoxib or etoricoxib tablet substances. Known hypersensitivity for sulphonamides. Active peptic ulcer or gastrointestinal haemorrhage. History of asthma, acute rhinitis, nasal polyps, angioneurotic oedema, urticaria or other allergic reactions after taking acetyl salicylic acid or NSAID including COX-2 inhibitors. Moderate/severe deranged liver function (Child-Pugh >7). Serum-creatinine clearance <30 ml/min. Inflammatory bowel disease. Heart failure (NYHA II-IV). Established ischaemic heart disease, peripheral arteriosclerosis and/or cerebrovascular disease, including previous myocardial infarction, angina pectoris, unstable angina, PCI or coronary bypass, previous transitory ischemic attack or apoplexia/stroke.

**iii) Exclusion criteria for H56:IC31:** Known hypersensitivity for vaccines or vaccine adjuvants.

**Investigational Product, Dose and Mode of Administration:**

**Arcoxia** (etoricoxib) tablets 120 mg, administered p.o. at 120 mg x 1 starting at the same time as initiation of anti-TB chemotherapy (study day 0) and for 20 weeks (day 0-140). If intolerable adverse reactions or clinical laboratory evaluation category 2 occur, dose will be reduced to 90 mg x1 or drug will be stopped.

**H56:IC31 vaccine;** administrated i.m at 5 µg 1st dose at study day 84 and 2nd dose at study day 140.

A phase I trial (C-032-456; open-label, dose-escalation of latent TB) and a phase I/IIa (C-035-456; randomized, placebo-controlled) with H56:IC31 show that the vaccine is well tolerated and no safety issues have been identified. A phase I/II clinical study of H56:IC31 (C-037-456) in patients treated for active pulmonary TB is ongoing in South-Africa. The first participant was dosed in January 2015 and after 12 first doses administered (19th February 2015) no safety concerns have been reported. Inclusion in study arm 3 and 4 will not start before all preliminary safety data from this study is available and the vaccine is proven safe also in this population.

**Study Duration:** Informed consent, inclusion, baseline assessments and start of standard anti-TB chemotherapy at day 0 followed by 20 weeks of study drug administration (day 0-140), 6 weeks (or according to clinical evaluation) of standard anti-TB chemotherapy alone (day 0-182) and follow-up control at day 210 and end of study visit day 238.

**Criteria for Evaluation:**

**Safety:** Tolerability and safety of etoricoxib and the therapeutic TB vaccine H56:IC31. Reductions of etoricoxib dose or stop of drug, AE/SAE/SUSAR including cardiovascular events, blood pressure, clinical chemistry and vaccine AE/SAE/SUSAR.

**Pharmacokinetics:** AUC, Cmax of etoricoxib at steady state after 7 days (Arm #1).

**Primary Immunogenicity readouts:**

1. Etoricoxib effect of TB specific immune responses: T cell proliferation and cytokine responses (change between day 0 and 140).
2. H56:IC31 vaccine immunogenicity: T cell proliferation and cellular cytokine responses 14 days post-immunization (day 98 and day 154).

3. Etoricoxib effect of H56:IC31 vaccine immunogenicity: T cell proliferation and cellular cytokine responses 14 days post-immunization (day 98 and day 154).

**Readouts:** 1. WB/PBMC ICS (cytokines responses). 2. T cell proliferation (cfse), 3. Tregs/maturity (CD25, FoxP3, COX-2). 4. Soluble biomarkers. 5. Monocyte responses (COX-2). 6. RNA analysis.

**Statistical Methods:** Non-parametrical methods to describe patient groups including matched pair statistics to determine primary endpoints within the four study arms.

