## Priority ranking of immunogenicity readouts according to statistical plan

### Definition of outcomes described in Tables 1-3

- **Sin cytokine:** Cells expressing only one cytokine: sin\_IFN $\gamma$  or sin\_IL2 or sin\_TNF $\alpha$ .\*
- **Duo cytokine:** Cells expressing two cytokines simultaneously: duo\_IFN $\gamma$ /IL2 or duo\_IFN $\gamma$ /TNF $\alpha$ \*or duo\_IL2/TNF $\alpha$ .\*
- **Tri cytokines:** Cells expressing three cytokines simultaneously: tri\_IFN $\gamma$ /IL2/TNF $\alpha$ .\*
- **Tot cytokines:** SUM of cytokine combinations expressing cytokine of interest (sin\_cytokines PLUS duo\_cytokines PLUS tri\_cytokines\*): tot\_IFN $\gamma$  or tot\_IL2 or tot\_TNF $\alpha$ \*
- **All cytokines for Whole Blood ICS (Cytokine+):** SUM of the following cytokine combinations: tot\_IFN $\gamma$  PLUS duo\_IL2/TNF $\alpha$  PLUS sin\_IL2 PLUS sin\_TNF $\alpha$ .
- **All cytokines for Fluorospot (Cytokine+):** SUM of the following cytokine combinations: tot\_IFN $\gamma$  PLUS tot\_IL2 MINUS duo\_IFN $\gamma$ /IL2.:

**Supplementary Table 3.** Hierarchal ranking of primary and secondary priority outcomes and definition of hypotheses that will be tested comparing etoricoxib vs. controls. Formal testing will be performed on the primary priority outcomes only, tertiary priority outcomes are not listed here.

| Method                                           | Outcome/readout                                                             | Time interval (days) | Comparison           |
|--------------------------------------------------|-----------------------------------------------------------------------------|----------------------|----------------------|
| Primary priority                          |                                                                             |                      |                      |
| FLUOROSPOT (FS)                                  | All_cytokine responses to SUM (Ag85+ESAT6+CFP10)                            | 0-84                 | Group (1+4) vs (2+3) |
|                                                  | Tot_IFN $\gamma$ responses to SUM (Ag85+ESAT6+CFP10)                        | 0-84                 | Group (1+4) vs (2+3) |
| Whole blood (WB) intracellular cytokine analyses | All_cytokine CD4 responses to PPD                                           | 0-84                 | Group (1+4) vs (2+3) |

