### IFN $\gamma$ +IL2+ responses to Ag85B and ESAT-6

[figure not shown]

red=Etoricoxib, blue=H56:IC31, black=Controls, green=Etoricoxib+H56:IC31

**Supplementary Figure 4. Cytokine responses for all study groups at all time points.** Descriptive line plots of different cytokine responses measured by Fluorospot at day 0 to day 238 with median and IQR for all study groups; etoricoxib-group (red; n=10), H56:IC31-group (blue, n=12), controls (black, n=10) and etoricoxib+H56:IC31 group (green, n=8) are depicted for Cytokine+ T-cells to individual *Mtb*

peptides (ESAT-6, Ag85B and CFP-10) (first 3 panels), IFN $\gamma$ +IL2+ T-cells in response to ESAT-6+Ag85B+CFP-10 (fourth panel) and ESAT-6+Ag85B (sixth panel) and finally IFN $\gamma$ + T-cells in response ESAT-6+Ag85B.

Supplementary Figure 5

a

[figure not shown]

b

[figure not shown]

[figure not shown]

**Supplementary Figure 5. Immunogenicity of the H56:IC31 vaccine.** Effect of the H56:IC31-vaccine administered at two doses (day 84 and day 140) on vaccine-induced immunity in the H56:IC31 group (blue, n=12) and controls (grey, n=10) (Hypothesis 2, table 3) at day 84 and day 154. Cytokine responses (IFN $\gamma$  and IL-2) to H56 fusion protein and the individual peptides (ESAT-6 and Ag85B) are measured by Fluorospot assay. **a** IFN $\gamma$  T-cell responses to the H56 fusion protein in the H56:IC31 group and controls at day 84 (n: 12/10) and day 154 (n: 11/10). Boxplots are shown with median, interquartile ranges (IQR) and minimum/maximum values. Median regression with treatment as only independent explanatory factor was applied for immunogenicity read-outs pre-assigned a hierarchical order to compensate for lack of multiple testing adjustments. Effect estimates of primary priority and 95% confidence intervals based on 1000 bootstrap replications and corresponding two-sided p-values depicted in Table 3 (main paper) and denoted in **a**. **b** Descriptive line plots with median and IQR, and individual trajectories at different time points during follow-up for both H56:IC31 and control group.

## Supplementary Figure 6

[figure not shown]

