### **1.3.3 COX-2i improves TB specific immune responses and regulation *in vitro***

Functional studies on the effect of COX-2i upon immune cells, longitudinally collected from clinically characterized TB patients during therapy at our hospital and from our national partners, are currently in progress in our lab. We have previously described elevated levels of Treg subsets in active and latent TB (10). In studies of active TB patients during anti-TB chemotherapy we demonstrate a decrease in the fraction of *Mtb*-specific IFN- $\gamma$ -producing T cells stimulated by TB-specific antigens (ESAT-6, CFP-10) *in vitro* already after 2 weeks of efficient treatment, whereas the pool of IL-2+ cells increased over time (30). The Treg was still able to expand after *Mtb*-specific *in vitro* stimulation, but a decline in activated Treg was seen when COX-i was added to the cells. These pilot findings indicate that COX-2i could possibly block regulatory T cells and improve TB specific immunity. In the current study these data will form the basis for additional in-depth exploratory analysis of Tregs in TB infection.

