#### 7.1.3 Primary immunogenicity Endpoints

1. Etoricoxib effect of TB specific immunogenicity: T cell proliferation and cytokine responses (change between day 0 and 140)

2. H56:IC31 vaccine immunogenicity: T cell proliferation and cytokine responses 14 days post-immunization (day 98 and day 154 compared to day 84)
3. Etoricoxib effect of H56:IC31 vaccine immunogenicity: T cell proliferation and cytokine responses 14 days post-immunization compared to H56:IC31 alone.

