## **10.4 Statistical Analysis**

Groups will be compared with non-parametrical statistical methods throughout with two-ways tests using p-values equal to or below 0.05 as significant. No adjustments due to multiple comparisons will be performed.

Deviation from the original statistical plan will be described and justified in the Clinical Study Report. The investigators can make the decision regarding individual values belonging to a subject to be excluded from the statistical evaluations, but only when a protocol violation is considered to weaken any of the scientific aspects of the study. Missing data will not be substituted by estimated values, but will be treated as missing data by the method used.

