##### **10.4.6.1 Primary Immunogenicity endpoints**

The primary variables of interest for assessment of immune response to vaccine will be the percentage of CD4+ and CD8+ T cells that produce any of selected cytokines. The immunogenicity of H56:IC31 in this study will be evaluated by PBMC ICS, T-cell proliferation and IL-2/IFN- $\gamma$  ELISPOT. Due to the exploratory nature of immunogenicity endpoints, the primary evaluation will be based on descriptive summaries and no formal hypothesis testing will be performed.

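### The protocol gives three incompatible rules for analysing the primary immunogenicity readouts, and the within-arm paired rule in the synopsis cannot separate a product effect from the effect of chemotherapy

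*Protocol*

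**What the plan says.** Three statements in the protocol itself cover the same readouts.

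- **Synopsis, Statistical Methods:** "matched pair statistics to determine primary endpoints within the four study arms". The primary objective in Section 2 is safety, so this phrase must refer to the primary immunogenicity readouts listed just above it.
- **Section 10.4:** "Groups will be compared with non-parametrical statistical methods throughout", with "two-ways tests using p-values equal to or below 0.05 as significant" and no multiplicity adjustment.
- **Section 10.4.6.1:** "the primary evaluation will be based on descriptive summaries and no formal hypothesis testing will be performed".

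Section 7.1.3 defines the first readout, the etoricoxib effect, as "T cell proliferation and cytokine responses (change between day 0 and 140"). No comparator is named there or for the second readout. The third readout names H56:IC31 alone as its comparator.

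On the background trend, Section 1.3.3 reports that during anti-TB chemotherapy the fraction of TB-specific IFN-gamma-producing T cells had already dropped by two weeks, "whereas the pool of IL-2+ cells increased over time". Section 3 gives chemotherapy to all four arms through day 182.

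The supplementary material is a later layer. It says it follows a statistical plan finalised on 16 March 2020, whereas the protocol is version 6.0 of October 2016. For Supplementary Tables 3 to 5 it states "Formal testing will be performed on the primary priority outcomes only", uses between-group median regression, and sets the etoricoxib window at day 0 to 84. The legends to Supplementary Figures 5 and 6 describe the readouts as "pre-assigned a hierarchical order to compensate for lack of multiple testing adjustments".

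**The concern.** The three protocol statements differ on whether anything is tested and on what is compared with what. The same data could give a significant etoricoxib change under the synopsis, a null group comparison under Section 10.4, and no test at all under Section 10.4.6.1.

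The synopsis version has a further fault. A paired test within an arm asks whether the readout moved. On the protocol's own evidence it moves under chemotherapy without any study product. A before-after change in arm 1 therefore cannot be read as an etoricoxib effect, and no within-arm test can answer the third readout, which is a contrast between two arms.

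**Working it through.** **1. What each rule estimates.** Let C be the mean change due to chemotherapy over the window and E the added change due to etoricoxib.

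- Within arm 1: expected change = C + E. The paired test has null hypothesis C + E = 0.
- Arm 1 minus arm 3: (C + E) − C = E.

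Only the second isolates E. The first does so only if C = 0, which Section 1.3.3 contradicts for IFN-gamma and IL-2 readouts.

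**2. False-positive rate when E = 0.**

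Inputs from the protocol: 10 patients per arm (Section 4.2); two-sided level 0.05 (Section 10.4); non-parametric tests (Section 10.4). Assumption: a common chemotherapy shift of d standard deviations of the within-patient change, normally distributed. The documents give no value for d, so a range is shown. There were 6,000 simulated trials per value; the simulation standard error is at most √(0.25/6000) = 0.65 percentage points.

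| Assumed d | Within-arm signed-rank test | Between-arm rank-sum test of change |
|---|---|---|
| 0 | 5% | 5% |
| 0.3 | 13% | 5% |
| 0.5 | 28% | 4% |
| 0.8 | 60% | 5% |
| 1.0 | 78% | 4% |
| 1.5 | 98% | 4% |

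As a check with a paired t-test, the noncentrality is d × √10, which is 1.58 at d = 0.5 and 3.16 at d = 1. The noncentral t distribution then gives 29% and 80%, in line with the simulation.

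**3. The ranking in the supplement.** Primary-priority rows number 4 (Supplementary Table 3) + 5 (Table 4) + 5 (Table 5) = 14. No passage gives a stopping or gating rule, so each is tested regardless of the others. The level used here, 0.05 per test, is taken from Section 10.4.

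- If independent: 1 − 0.95^14 = 0.51 chance of at least one false positive (1 − 0.95^4 = 0.19 for the first family, 1 − 0.95^5 = 0.23 for each of the others).
- With an assumed equal correlation within each hypothesis of 0.3, 0.5, 0.7 or 0.9, and independence between hypotheses (200,000 simulations): 0.48, 0.44, 0.37 or 0.27.

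**4. Precision given up.** In SD units of change, with a normal approximation for a mean and planned numbers, the 95% half-widths are:

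- one arm of 10: 1.96 × √(1/10) = 0.62
- 10 versus 10: 1.96 × √(1/10 + 1/10) = 0.88
- arms 1+4 versus 2+3, 20 versus 20: 1.96 × √(1/20 + 1/20) = 0.62

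**The case against.** The strongest reply is that this is an exploratory phase I trial with safety as its primary objective and no sample size calculation, so loose wording on secondary readouts does little harm. The synopsis sentence is about describing patient groups, it covers the control arm too, and it never says that a within-arm p-value establishes a product effect. The supplement in fact describes between-group analysis, and the legend to Supplementary Figure 3 treats all p-values as hypothesis-supporting, not confirmatory.

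Much of this stands, and it rules out several stronger readings.

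- A reader might infer that the sponsor will credit chemotherapy changes to the products. The documents do not say so. They leave it open, because the synopsis has the paired statistics determine the endpoints and the first two items of Section 7.1.3 name no comparator.
- A reader might count the supplement's 14 tests and its day 0 to 84 window as further contradictions within the protocol. They belong to a later specification, and Section 10.4 provides for justified deviations from the plan.
- A reader might quote 51% as the error rate. That assumes independence, yet total IFN-gamma is by definition part of the all-cytokine readout on the same assay and antigens. It is the top of a range, and it bears on interpretation, not on a failed confirmatory claim.
- A reader might argue that arms 1 and 4 cannot be pooled at day 140. No passage pools them there, and against arms 2 and 3 the contrast would be balanced for vaccination. It would only average over any etoricoxib-vaccine interaction.

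The size of the shift is also uncertain. IFN-gamma and IL-2 are reported to move in opposite directions, so a readout counting cells with any selected cytokine could move less than either alone.

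None of this removes the conflict between the synopsis, Section 10.4 and Section 10.4.6.1. Exploratory status does not tell an analyst which of the three to follow.

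**Conclusion.** The point holds for the three protocol statements and for the unsuitability of the within-arm rule. With no product effect, that rule's false-positive rate runs from the nominal 5% at no chemotherapy shift to about 28% at 0.5 SD and 78% at 1 SD, against 4 to 5% between arms. These figures rest on 10 patients per arm, normal changes and an assumed shift. The problem is greatest for the etoricoxib change from day 0. It is weaker for vaccine changes from day 84, although chemotherapy continues to day 182.

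The between-arm remedy assumes that the arms share the chemotherapy trend. Arms 2 and 4 are enrolled in successive stages (Section 3), so for that pair this is an assumption and not a product of concurrent randomisation.

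The multiplicity part is a matter of wording. A ranking without a gate does not compensate for unadjusted testing, and the chance of at least one false positive is roughly 27 to 51%. That does not make gated testing obligatory for exploratory readouts; it is one option, with a loss of power for lower-ranked readouts.

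**What to change.** 1. In the synopsis and Sections 7.1.3, 10.4 and 10.4.6.1, state one rule: product effects on immunogenicity are judged only by between-arm comparison of change, reported as estimates with 95% confidence intervals and treated as exploratory. Within-arm changes are descriptive.
2. Name the comparison arms for each of the three readouts in Section 7.1.3.
3. State one etoricoxib window. Day 0 to 84, used in the later supplement, is the one that ends before any vaccination; Section 7.1.3 and the synopsis currently have day 0 to 140.
4. Remove the significance label in Section 10.4 for these readouts, and delete the statement in the legends to Supplementary Figures 5 and 6 that the ranking makes up for the missing adjustment. The ranking can stay as an order of importance.

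The cost is wording only, with no new data or patients. Within-arm results lose their inferential role, and a comparison of two arms of 10 has intervals about √2 = 1.4 times as wide as a single-arm change (0.88 against 0.62 SD). At the planned 20 versus 20, the pooled day 0 to 84 comparison gives back that width.
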